#### 2.3.4. Study Intervention

The study intervention, SPARKED, is a brief FPE that will be delivered via telehealth using the SPARKED guide developed in Study Phase 1. The guide will contain information on predetermined topics organised into modules for each psychoeducational session, which will be conducted biweekly at Weeks 2, 4, and 6 from enrolment. A six-week follow-up at Week 12 will primarily focus on assessing the retrospective acceptability of SPARKED. The key features of the SPARKED protocol are shown in Table 1.

The sessions will be tailored to enhance participants’ understanding of MDD and its treatment, coping strategies, self-efficacy skills, and early signs of relapse, empowering them to take an active role in their treatment decision-making. Only one member of the research team will facilitate all SPARKED sessions to ensure consistency throughout the sessions. During each session, evidence-based information will be provided, and participants will be encouraged to seek further discussion and clarification as needed.

#### 2.3.5. Study Procedure

Patients with MDD who are interested in the study can contact the research team using the contact details on the study flyers for more information or to express interest. If the participants meet the eligibility criteria, a face-to-face meeting will be scheduled with each single-family dyad to provide them with detailed information about the study, explain the consent process, and distribute participant information sheets. The meetings will be held either at the primary healthcare setting where participants are recruited or in meeting rooms within community halls, depending on participants’ preferences. In addition, suicide risk assessments of individuals with MDD will be conducted using the suicide risk screening tool [50]. If imminent risk is identified, individuals will be supported with a stepped-up care referral. Written consent will be obtained from each eligible participant before they are enrolled in the study.

All baseline assessments will be conducted immediately after enrolment. Basic sociodemographic data, along with medical and medication histories, will be collected from individuals with MDD. Similarly, sociodemographic information will be obtained from the participants’ family members or significant others. Upon completion of the pre-intervention assessments, the initial SPARKED telehealth session will be scheduled. Participants will select their preferred telehealth method (videoconferencing or telephone call) based on their individual circumstances, as well as a secure environment for each session. Subsequent sessions will be scheduled at the end of each session. The Zoom platform will be utilised for videoconferencing; however, participants’ preferences for an alternative platform will be considered. Reminder messages or phone calls, based on participants’ individual preferences, will be used to remind them of their upcoming session. To reduce the risk of incomplete intervention, the family member or significant other supporting the individual with MDD will remain consistent throughout the study.

A contingency plan to prevent dropout includes offering flexible session scheduling, allowing participants to choose their preferred telehealth modality, and providing phone credits for each session, along with modest tokens to compensate for their time. Participants will be advised that they can reschedule a session if necessary. Subsequently, a new session will be organised. In addition, reminder phone messages or calls, according to participants’ preferences, will be made one to two days prior to each scheduled session.

Participants will complete the second and third sets of outcome measurements immediately after the intervention (Week 6) and at follow-up (Week 12), respectively. Measures can be completed on hard copies and mailed to the research team using prepaid envelopes provided by the team or completed online. Additionally, SSIs will be conducted with each patient–family member dyad at follow-up to collect feedback on the intervention. All FPE sessions and the SSIs will be audio recorded with participants’ consent, allowing the research team to conduct checks on adherence to the intervention guide and protocol. Field notes will be maintained at all sessions.

#### 2.3.7. Outcome Measures

##### Primary Outcomes

The primary outcomes are the feasibility of delivering SPARKED through telehealth and its acceptability among study participants. The feasibility-related outcomes include:Recruitment rate: The main feasibility outcome of this study is the recruitment rate, which was referred to in the sample size calculation. The recruitment rate is defined as the percentage of eligible participant dyads who consented to participate in the study. The observed proportion (E) will be described based on the following pre-defined thresholds: the trial is feasible (if E ≥ 70%); the trial may be feasible, so proceed with caution (if E falls between 33 and 70%); and the trial is unfeasible to proceed (E ≤ 33%).Retention rate: This is defined as the percentage of participants who remain in the study throughout the entire study period, from enrolment to follow-up (Week 12). The observed proportion (E) will be described in the same way as the recruitment rate.Outcome measure return rate: Defined as the percentage of participants who return filled-out self-report measures at enrolment, immediately post-intervention (Week 6), and at follow-up (Week 12).Outcome measure completion rate: Defined as the percentage of participants who successfully complete each secondary outcome measure at enrolment, immediately post-intervention (Week 6), and at follow-up (Week 12).

The acceptability-related outcomes will be assessed at three time points: pre-intervention (prospective acceptability), during intervention delivery (concurrent acceptability), and post-intervention (retrospective acceptability), in line with the theoretical concept of acceptability of a healthcare intervention postulated by Sekhon et al. [53].

Prospective acceptability-related outcome: The number of eligible participants who consented to study participation.Concurrent acceptability-related outcome: The number of SPARKED sessions attended and the reasons for dropout during the study period, from enrolment to the follow-up (Week 12).Retrospective acceptability-related outcome: Feedback on SPARKED delivered via telehealth will be assessed through SSIs using an SSI guide (Supplementary Material, Table S4) at follow-up (Week 12).

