#### 2.3.3. Participants and Sample Size

Patient–family member dyads will be recruited through study flyers or a GP- or nurse practitioner-informed referral pathway.

Inclusion criteria are as follows: (i) an adult (aged 18 years or older) diagnosed with MDD who has been prescribed at least one antidepressant medication for treating the disorder and can provide a formal record of a current prescription, (ii) an adult with MDD who does not have any other serious mental or physical illness, (iii) an adult with MDD who has an adult family member, a carer, or significant other supporting themat home, and (iv) both the adult with MDD and their support person consent to participate in the study.

Exclusion criteria are: (i) an adult with MDD whose family member, carer or significant other cannot participate in the study, (ii) an adult family member of an adult with MDD who declines to participate, (iii) an adult with MDD identified with high suicide risk or current suicidal ideation using a suicide risk assessment tool [50], and (iv) an adult with MDD or a family member with a serious mental or physical health condition, cognitive impairment, or hearing impairment without a hearing aid. These health conditions may affect an individual’s ability to participate effectively in telehealth sessions.

The SS-PROGRESS WebApp (SS-PROGRESS) [51] was used to calculate the sample size required for the binary feasibility outcomes for estimation and hypothesis testing of pro-gression criteria. The 1-sample 1-tailed binomial exact test tests the null hypothesis that the true feasibility outcome is not greater than the upper “RED” stop limit [52]. Assuming an alpha of 0.05 and a beta of 0.2, we applied a minimum value of acceptable feasibility of 34% (indicating the smallest percentage for an outcome, which suggests that the main study would be feasible) and an expected value of 70% for each feasibility objective, resulting in a minimum sample size of 13.

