#### 2.3.9. Quality Assurance and Data Analysis

The study team will undertake quality assurance activities as previously outlined in Section 2.2.3. Data analysis will include both descriptive and inferential statistics.

Outcomes related to feasibility and acceptability (both prospective and concurrent) will be presented as either absolute or relative counts. Data collected through the SSIs (retrospective acceptability data) will undergo thematic analysis following the same procedure outlined in Study Phase 1. Codes and themes identified through this process will be used to refine the SPARKED guide and protocol for future large-scale trials. Conversely, data from each outcome measure will be prepared according to the developer’s instructions. Missing data will be handled using the pairwise deletion method, where missing data are omitted on an analysis-by-analysis basis. Given the small sample size, the Friedman test (significance level of 0.05) will be used to assess whether there are significant differences in the means of outcome measurements across the three measurement time points. The results of this analysis are entirely exploratory research findings.

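### The progression bands are not the exact test on which n = 13 was sized, so the stated alpha and power do not describe the progression decision

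*Protocol article*

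**What the plan says.** I call the three bands RED, AMBER and GREEN; the protocol article itself uses only the first name.

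- **Section 2.3.3 (sample size).** The one-sample, one-tailed exact binomial test "tests the null hypothesis that the true feasibility outcome is not greater than the upper" RED stop limit. The error rates are given as "Assuming an alpha of 0.05 and a beta of 0.2". The inputs are 34% ("we applied a minimum value of acceptable feasibility of 34" per cent) and "an expected value of 70% for each feasibility objective, resulting in a minimum sample size of 13". The section says the calculation serves both estimation and hypothesis testing of the progression criteria.
- **Section 2.3.7 (Primary Outcomes).** Recruitment rate is the main feasibility outcome and is tied to the sample-size calculation. It is graded by comparing the observed proportion E with fixed limits. GREEN is 70% or more. AMBER is "the trial may be feasible, so proceed with caution (if E falls between 33 and 70" per cent. RED is "the trial is unfeasible to proceed (E ≤ 33" per cent. Retention is graded in the same way. The denominator for recruitment is eligible dyads, and their number is not stated.
- **Section 2.3.9 (analysis).** Feasibility outcomes "will be presented as either absolute or relative counts". The only test named there, the Friedman test, is for the secondary outcome measures.

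**The concern.** The test that produced n = 13 has a critical value, and neither band edge equals it. A result can therefore leave RED and be graded AMBER without the test having rejected RED. The 5% and 20% error rates belong to a test that section 2.3.7 does not use for grading and section 2.3.9 does not report.

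The recruitment and retention rates are meant to inform a later randomised trial. A reader who sees alpha 0.05 in section 2.3.3 and an AMBER grade in the results may believe that RED has been ruled out at the 5% level. A reader who sees 80% power may believe that a true rate of 70% will usually be graded GREEN. Neither is so. If this is settled only after the data are in, a result of 5 to 7 of 13 could be argued either way.

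**Working it through.** **Inputs.** Alpha 0.05 one-sided, beta 0.2, expected rate 70%, minimum acceptable rate 34% (section 2.3.3); RED at 33% or less, GREEN at 70% or more (section 2.3.7). X is the number of successes out of n, taken as binomial with true rate p.

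**Step 1: reproduce n = 13.** For each n, find the smallest r with P(X ≥ r | p0) ≤ 0.05, then compute the power P(X ≥ r | 0.70).

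| n | r | Error at 33% | Error at 34% | Power at 70% |
|---|---|---|---|---|
| 11 | 7 | 0.0366 | 0.0430 | 0.7897 |
| 12 | 8 | 0.0176 | 0.0213 | 0.7237 |
| 13 | 8 | 0.0326 | 0.0390 | 0.8346 |

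No n from 8 to 12 reaches 80% power, so 13 is the first in that range. The stated figure is correct whether the null is 33% or 34%. The test rejects RED at 8/13 = 61.5% or more.

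**Step 2: translate the bands to n = 13.** 4/13 = 30.8% and 5/13 = 38.5%, so RED is X ≤ 4. 9/13 = 69.2% and 10/13 = 76.9%, so AMBER is X = 5 to 9 and GREEN is X ≥ 10. The results 5, 6 and 7 are AMBER but below the critical value of 8.

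**Step 3: operating characteristics at n = 13.**

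| True rate | Leaves RED, P(X ≥ 5) | Test rejects RED, P(X ≥ 8) | GREEN, P(X ≥ 10) |
|---|---|---|---|
| 20% | 0.099 | 0.001 | below 0.001 |
| 25% | 0.206 | 0.006 | below 0.001 |
| 30% | 0.346 | 0.018 | 0.0007 |
| 33% | 0.438 | 0.033 | 0.0015 |
| 70% | 0.996 | 0.835 | 0.421 |

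For example, at 33%: P(X ≤ 4) = 0.5624, so P(X ≥ 5) = 1 − 0.5624 = 0.4376. At 70%, AMBER has probability 0.996 − 0.421 = 0.575.

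**Step 4: other denominators.** Recruitment is counted over eligible dyads. Assuming a fixed number of these from 13 to 40, the chance of leaving RED at a true 33% ranges from 0.438 (n = 13) to 0.585 (n = 15), and is 0.452 at n = 40. If recruitment instead stops once 13 dyads have consented, the rate leaves RED when at most 39 eligible dyads were needed (13/39 = 33.3%, 13/40 = 32.5%). The chance of that equals P(X ≥ 13 | n = 39, p = 0.33) = 0.542.

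**The case against.** **44% is a boundary value.** This stands: the figure falls to 35% at a true 30%, 21% at 25% and 10% at 20%. It must be quoted as the value at the RED limit, not as a general rate for infeasible trials. The nominal 5% is also a boundary value, so comparing the two at 33% is like for like.

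**AMBER is a caution, not a declaration of feasibility.** This also stands. A reader might infer that an infeasible trial would be called feasible 44% of the time. The documents do not support that: only GREEN is worded as feasible, and a false GREEN at 33% has probability 0.15%. Nor does section 2.3.7 say that AMBER means RED has been rejected. The gap is that section 2.3.3 states error rates for progression criteria, and no grade in section 2.3.7 has them.

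**13 is not the recruitment denominator.** Agreed; 5/13, 8/13 and 10/13 suit retention. Step 4 shows that the size of the problem does not shrink for recruitment.

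**33% and 34% might be read as a contradiction.** They need not be: RED up to 33% with 34% as the smallest acceptable whole percentage is coherent. Neither n = 13 nor the cut-off of 8 depends on the choice.

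**A separate analysis plan may hold the test.** It may, and the absence of further detail is not the complaint. The article itself fixes the grading rule and the form of reporting, and these do not match its sample-size basis.

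**Conclusion.** The mismatch is real. The sample size of 13 is correct for the stated test, but alpha 0.05 and 80% power are properties of rejecting RED at 8 of 13, not of the bands. At n = 13 the bands leave RED with probability 44% when the true rate is exactly 33%, against 3.3% for the sized test. They reach GREEN with probability 42% when the true rate is 70%, against 83.5% power for the sized test.

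These figures assume independent dyads with a common rate and a denominator of 13. For recruitment, assumed denominators of 13 to 40 give 44% to 59% at the RED limit.

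A reader might go further and infer that AMBER below the critical value ought to mean stopping. The documents do not settle that. A rule of not progressing at 7 of 13 or fewer would apply 71% of the time at a true 50% (1 − 0.2905), a rate the protocol article places in AMBER.

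**What to change.** Keep the bands and the sample size, and amend sections 2.3.7 and 2.3.9 as follows.

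1. For recruitment and retention, report the one-sided exact binomial test against the RED limit beside the band, using the critical value for the actual denominator: 8 if it is 13, or 11 if it is 19.
2. Give a matching one-sided 95% exact lower bound, or equivalently a 90% two-sided interval. A two-sided 95% interval would not match the test: at 8/13 its lower limit is 31.6%, below RED, although the test rejects; the one-sided bound is 35.5%.
3. Label AMBER results below the critical value as not ruling out RED. How to act on them is for the investigators to decide, before data are seen.
4. State that alpha 0.05 and 80% power refer to rejecting RED, not to leaving the RED band or reaching GREEN.
5. Word the RED limit consistently in both sections and say which value is the null. This changes nothing at 13, but at some other denominators it moves the critical value by one (at 16 it is 9 for 33% and 10 for 34%).

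The cost is a few lines of text and analysis, no extra participants, and a less favourable label for some AMBER results.

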##### Secondary Outcomes

Four secondary outcomes will be measured at baseline, immediately after the intervention, and at the six-week follow-up using validated instruments. These outcomes are exploratory and will not inform a future RCT.

Personal recovery among patients: This outcome refers to subjective recovery, which will be assessed using the Recovery Assessment Scale-Domains and Stages (RAS-DS), a 38-item self-rated measure of personal recovery [54]. Studies have shown that RAS-DS is relevant to recovery [55] and demonstrates good reliability and validity, reflecting mental health recovery [56].Severity of depressive symptoms among patients: This outcome will be measured using the Patient Health Questionnaire-9 (PHQ-9), a nine-item self-administered tool [57]. The choice of PHQ-9 is based on evidence supporting its reliability and validity for assessing depression severity [58].Adherence to antidepressant medication among patients: Antidepressant adherence will be assessed using the Medication Adherence Report Scale-5 (MARS-5, ©[name]), a five-item self-administered instrument that measures both intentional and unintentional nonadherence behaviours [59]. Studies show that MARS-5 is a reliable and valid adherence measure [59,60]. Besides, the wording in MARS-5 is non-judgmental, which may reduce the tendency to underreport medication nonadherence due to social desirability [59].Medication Necessity Beliefs and Concerns among patients: Patients’ necessity beliefs and concerns about antidepressants will be assessed using the Beliefs about Medicines Questionnaire (BMQ)-Specific 11 (BMQ-Specific 11, © [name]) [61]. This instrument comprises two scales: Specific-Necessity and Specific-Concerns [61] and has been reported as an effective tool for identifying patients at risk of medication nonadherence [62], which may be useful in developing interventions to address nonadherence.

#### 2.3.8. Risk Mitigation Plan and Data Management

Risk mitigation plan for managing participant distress includes suicide risk screening (as previously mentioned in Section 2.3.5) and collaborative development of personalised safety plans [63] during the recruitment process, in addition to monitoring adverse effects. The safety plan will outline a participant’s warning signs of an imminent crisis, distress-coping strategies, and available helpful resources, including supportive social networks. It will also include contact details for the participants’ primary healthcare provider (if provided by the participant), the local mental health helpline and emergency services for stepped-up care. Escalation of care will be prioritised once distress is reported or observed, triggering the use of the safety plan. The interventionist will employ empathetic and therapeutic communication skills to minimise further distress and maintain a trusting relationship with the participants.

All research materials will be stored in a lockable cabinet with restricted access. Electronic data will be password-protected and securely stored on the institutional OneDrive, accessible solely to members of the primary research team. Participants will be informed about the importance of utilising private space during SPARKED sessions and post-intervention SSIs. To ensure access to a private internet source during SPARKED sessions and SSIs, each dyadic participant will be offered 2 GB of data per session. Serial numbers will substitute participants’ details to ensure anonymity, and all research outputs will be devoid of any personally identifiable information relating to participants.

In accordance with the International Council for Harmonisation Guideline for Good Clinical Practice [64] and the ethical approval for this research, the research team will conduct ongoing safety assessments, including the monitoring and reporting of adverse effects to the relevant ethics committees. Furthermore, measures implemented to address these adverse effects will be duly reported to the ethics committees.

#### 2.3.9. Quality Assurance and Data Analysis

The study team will undertake quality assurance activities as previously outlined in Section 2.2.3. Data analysis will include both descriptive and inferential statistics.

Outcomes related to feasibility and acceptability (both prospective and concurrent) will be presented as either absolute or relative counts. Data collected through the SSIs (retrospective acceptability data) will undergo thematic analysis following the same procedure outlined in Study Phase 1. Codes and themes identified through this process will be used to refine the SPARKED guide and protocol for future large-scale trials. Conversely, data from each outcome measure will be prepared according to the developer’s instructions. Missing data will be handled using the pairwise deletion method, where missing data are omitted on an analysis-by-analysis basis. Given the small sample size, the Friedman test (significance level of 0.05) will be used to assess whether there are significant differences in the means of outcome measurements across the three measurement time points. The results of this analysis are entirely exploratory research findings.

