## 4. Discussion

This protocol details the co-design strategies and feasibility assessment of SPARKED, a family psychoeducational intervention for MDD, delivered through telehealth. This study will also examine the preliminary effects of SPARKED on both clinically related outcomes (antidepressant adherence and depression severity) and non-clinically related outcomes (medication necessity beliefs and concerns, as well as personal recovery). The results on these outcomes will indicate the direction of an effect and will not be used to determine an effect size for a sample size calculation in a subsequent fully powered trial.

Major depressive disorder is a debilitating mental health condition that significantly impacts an individual’s life and, consequently, their family [65], thereby contributing to the burden of MDD. The impact of MDD is further compounded, given that residual depressive symptoms may persist even after remission [66] and potentially impair global functioning [67]. Even so, research indicates high rates of nonadherence to antidepressant treatment [68,69], despite evidence supporting its efficacy [70] and effectiveness [71] compared to placebos. A study conducted among patients from the United States and five European countries revealed that antidepressant nonadherence persisted longer due to a lack of belief in the necessity for the medication [72]. Thus, ensuring that individuals who opt for antidepressant treatment are adequately informed to make informed decisions regarding their treatment and feel empowered to discuss their choices with their healthcare providers is of paramount importance.

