### 4.2. Limitations

This protocol has some limitations. The six-week post-intervention follow-up period is relatively short, as the study’s primary aim is to assess the feasibility of the intervention and data collection methods before conducting a larger trial with a longer follow-up. As such, the study will not adequately capture the long-term effects of SPARKED. Next, the feasibility study phase focuses on patient-related outcomes. Evaluating outcomes among family members could have offered an opportunity to ascertain whether SPARKED influences outcomes for both patients and their families. In addition, the small sample size will not permit the evaluation of the intervention’s effect size. Consequently, this study cannot draw strong conclusions regarding the effects of SPARKED. A large-scale RCT of SPARKED will be required to determine the effectiveness of the intervention. Next, the exclusion criteria regarding individuals who are assessed to have imminent suicidal risks limit the generalisability of SPARKED. To improve the generalisability of this research, future studies should consider implementing strategies to optimise contacts with participants for monitoring and assessing suicide risks, as well as establishing a pathway for escalated care. Finally, using telehealth to deliver SPARKED might inadvertently exclude people who lack access to digital devices or digital skills. While this research will report all technical challenges encountered during the study (context-related) to help tailor solutions for future research, future studies should consider providing an easy-to-understand graphic guide on how to use devices or offering in-person support for participants to address this limitation.

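### Section 2.3.9 describes the Friedman test as a comparison of means; it compares within-patient ranks, gives no direction, and uses only patients with all three visits

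*Protocol article*

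**What the plan says.** Section 2.3.9 plans one named inferential procedure for the secondary outcomes, chosen because the sample is small: "the Friedman test (significance level of 0.05) will be used to assess whether there are significant differences in the means of outcome measurements" over the three time points. The same paragraph gives the missing-data rule, "Missing data will be handled using the pairwise deletion method, where missing data are omitted on an analysis-by-analysis basis", and labels the results exploratory. It names no follow-up contrast, change score or interval.

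The Discussion (section 4) states the use: "The results on these outcomes will indicate the direction of an effect and will not be used to determine an effect size". Section 4.2 adds that "the small sample size will not permit the evaluation of" an effect size. Section 2.3.9 also mentions descriptive statistics, and section 3 plans a table of the secondary outcomes by measurement time point. Section 1 makes preliminary effects on these outcomes the secondary objective.

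**The concern.** Three things do not fit together.

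- **Hypothesis.** A rank test is described as a test of means. A report that follows the text would draw conclusions about mean scores from a statistic that does not address them.
- **Direction.** Direction is the declared use of the results, but the only inferential procedure named is an omnibus test with no sign.
- **Missing visits.** The term pairwise deletion suggests that a patient with two of three visits still contributes to the comparison of those two. In a standard three-visit Friedman test that patient is dropped for that outcome.

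What is at stake is how the secondary objective is reported. The progression thresholds concern recruitment and retention and are not affected.

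**Working it through.** **Inputs from the protocol article.** Three time points: baseline, Week 6, Week 12 (2.3.7). Minimum sample size 13 and expected value 70% for each feasibility objective (2.3.3). Retention counted from enrolment to Week 12 (2.3.7). Friedman test at 0.05 (2.3.9). The article states no power or sample size for the Friedman test.

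**The plan's own figure.** The 13 comes from a one-sided exact binomial test. With 13 patients and a cut-off of 8, the type I error at 34% is 0.039 and the power at 70% is 0.835; no smaller number meets both 0.05 and 0.80. So 13 reproduces, but it was set for binary feasibility outcomes.

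**Step 1: does the test compare means?** With n patients, k = 3 visits and visit rank sums R, the statistic is

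Q = 12 / [n·k·(k+1)] × ΣR² − 3·n·(k+1).

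Constructed example with n = 13: ten patients score 18, 15, 12 and three score 5, 15, 25.
- Means: (10×18 + 3×5)/13 = 15; 15; (10×12 + 3×25)/13 = 15. All equal.
- Rank sums: 10×3 + 3×1 = 33; 13×2 = 26; 10×1 + 3×3 = 19.
- Q = 12/156 × (1089 + 676 + 361) − 156 = 163.54 − 156 = 7.54; p = 0.023 on 2 degrees of freedom.

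The reverse also occurs. With 12 patients, means of 11, 11 and 8, and balanced ranks (rank sum 24 at each visit), Q = 12/144 × (3 × 576) − 144 = 0 and p = 1.00. The test can reject when means are equal and see nothing when they differ.

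**Step 2: does it show direction?** Give all 13 patients the same pattern of change at Weeks 6 and 12: −2 and −4 points, or +2 and +4, or −0.1 and −0.2. The rank sums are 13, 26 and 39 in some order each time, so Q = 12/156 × (169 + 676 + 1521) − 156 = 26.0 and p = 2.3 × 10⁻⁶ in all three cases. Improvement and deterioration give the same result.

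**Step 3: who enters the test?** Assume 13 are enrolled and every retained patient returns all three assessments.
- At 70% retention: 13 × 0.70 = 9.1 complete patients, so about 4 are dropped.
- If those patients miss only Week 12, a baseline-to-Week-6 comparison would keep all 13, against about 9 in the Friedman test.

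The article gives no return rate per visit. If each visit is returned independently (an assumption):

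| Return per visit | All three visits | A given pair |
|---|---|---|
| 90% | 13 × 0.9³ = 9.5 | 13 × 0.9² = 10.5 |
| 80% | 13 × 0.8³ = 6.7 | 13 × 0.8² = 8.3 |

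If the 13 are eligible rather than enrolled dyads, which the recruitment-rate definition would allow, about 13 × 0.7 = 9.1 would enrol and 9.1 × 0.7 = 6.4 be complete.

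**Step 4: what would paired changes give?** The half-width of a 95% confidence interval for a mean change, in SDs of change, is t(0.975, n−1)/√n:
- n = 13: 2.179/√13 = 0.60
- n = 9: 2.306/√9 = 0.77

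These intervals are wide, but the estimate has a sign and its uncertainty is visible.

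**The case against.** The strongest reply is that little depends on this. The outcomes are exploratory, and the Friedman test is a common choice for three repeated measures in a small sample. Contrasts and change estimates may well sit in a fuller protocol or analysis plan. That stands as a limit on severity. It does not rescue the word means, which the article itself states.

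Some stronger readings are tempting but not supported:

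- **That the deletion rule contradicts the test.** The article defines its rule as omission analysis by analysis. Dropping incomplete patients separately for each outcome fits that definition. The label misleads and the loss of data goes unacknowledged, but there is no strict contradiction.
- **That direction cannot be obtained at all.** The Discussion attributes direction to the results, not to the p-value, and the table planned in section 3 could show it. What is missing is any stated uncertainty alongside it.
- **That the test fails because it gives no effect size.** Sections 4 and 4.2 decline to use or evaluate one, so this is no failing of the plan.
- **That low power, completer bias or multiplicity show the plan to be unsound.** With 9 patients and an assumed shift of 0.5 SD, simulated power is about 24% at correlation 0.5 and 29% at 0.6, but the article claims no power here. An assumed link between Week 6 severity and dropout biases a completer-only Week 6 change by about −0.035 to −0.125 SD over a range of inputs, but no such estimate is planned. The 23% chance of a false positive (1 − 0.95⁵) assumes five independent tests and concerns results already labelled exploratory. These figures are illustrations only.
- **That the Friedman test must be replaced.** Replacing it, or using a version for incomplete blocks, is a preference.

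**Conclusion.** The point holds in a limited form. Section 2.3.9 states the wrong hypothesis for the Friedman test; that is a matter of fact and needs no assumption. The omnibus p-value does not serve the declared use, direction, which is left to a descriptive table with no stated uncertainty. The deletion rule amounts to complete-case analysis within each outcome: about 9 of 13 enrolled patients at the protocol's expected 70% retention, assuming that 13 are enrolled and every retained patient returns all three assessments. The number of baseline-to-Week-6 pairs lost depends on which visits are missed, up to about 4 if only Week 12 is missed.

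Severity is minor to moderate. The outcomes are exploratory, and neither the feasibility thresholds nor a later sample size rests on them.

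**What to change.** In section 2.3.9:

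1. Describe the Friedman test as an exploratory test of rank distributions across the three visits, not of means.
2. State that it uses patients with all three assessments of the given outcome, and report that number for each outcome.
3. For each score (RAS-DS, PHQ-9, MARS-5, BMQ-Necessity, BMQ-Concerns), also report the paired change from baseline to Week 6 and from baseline to Week 12 with a 95% confidence interval, using every patient who has that pair. Available-pair deletion has a real meaning here.
4. Base statements about direction on these changes and intervals, not on the Friedman p-value.

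The cost is one paragraph of text and ten simple estimates (five scores × two changes), with no new data. The intervals will be wide. Reporting them does not conflict with the article's statement that the results will not be used to size a later trial.
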